### Sample size and statistical power

The hospitals in Stockholm treat more than 100 extremely preterm infants every year, but several of them are not residents of Stockholm County, which is a prerequisite for study inclusion. The study team is prepared to recruit 130 participants, 50% of which will be randomized to the SPIBI intervention. The sample size is based on feasibility, and the assumption is that the effect size of the intervention on the primary outcome measure Emotional Availability Scales (EAS) will be moderate, i.e., Cohen’s d = 0.5. This is largely in line with the results of Flierman et al. [50] for the sensitivity scale of the EAS in the previously mentioned Dutch trial. Hence, we aim to recruit 130 participants, which gives us a power of 0.8 given a normal distribution and an alpha value of 0.05.

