### Outcome measurements

Since the SPIBI is a multi-professional intervention, the outcome is measured across several domains: outcomes concerning emotional availability in the dyadic relation, outcomes measuring child development and outcomes related to parental mental health and parenthood.

The *primary outcome* is the Emotional Availability Scales (EAS) [65], which will be used primarily at 12 months corrected age but then again at 24 months corrected age. The primary coder is blind to group allocation, whereas the second coder, who is used for interrater reliability checks in 20% of the cases, is not. The scale has four parental dimensions (sensitivity, structure, non-intrusiveness, and non-hostility) and two child dimensions (child responsiveness and child involvement). Each subscale has a maximum score of 29 and a direct score of 1–7. It is hypothesized that higher scores will be observed in the intervention group. Previous international studies have shown significant effects of parental sensitivity and structuring as well as child involvement [50], which also seem to be the subscales most indicative of maternal anxiety in the NICU [66].

The *secondary outcome measurements* are listed below. For measuring the cognitive, language, and motor development of the children, the Bayley Scales of Infant and Toddler Development, Third Edition (BSID-III) [67], will be used at 24 months corrected age. Composite scores are standardized to mean (SD) scores of 100 [15], based on age-matched normative data. The secondary hypothesis is that the mean will be higher in the intervention group.

The child’s executive function at 24 and 36 months corrected age will be measured with the Behaviour Rating of Executive Function, Parental Version (BRIEF-P) [68, 69]. All 5 subscales (*inhibit, shift, emotional control, working memory and plan/organize)* will be used, and the hypothesis is that the intervention group will have fewer executive problems reported.

Child’s motor development will be measured by the Alberta Infant Motor Scale (AIMS) [70, 71] at 3 and 12 months corrected age. The range of the AIMS is 0–58 points, with a hypothesis of higher scores for the intervention group.

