### Statistical analysis plan

Data will be analysed using intention to treat analysis for the primary outcome and separate testing with multiplicity adjustments for secondary outcomes. Data will be analysed using SPSS version 25 (IBM, New York) and reported according to the CONSORT statement for RCTs. Descriptive parametric statistics will be presented as percentage for categorical variables and as mean and SD for continuous variables such as age or centiles if the data is skewed. Comparisons between the two groups will be performed with Mann-Whitney U test for independent samples. Subgroups with additional analyses will also be used for detaching outcome differences according to number of home-visits in total, additional medical diagnoses and whether one or two parents participated in the intervention. The level of significance is specified at 0.05. To account for repeated measures, to model within-subject variance, and to handle correlated data of continuous variables a linear mixed model will be used. An interaction term will be introduced in the model to examine heterogeneity effect. For binary and ordinal outcome variables Generalized Estimating Equation (GEE) will be employed. For the main analysis no missing data will be imputed. However, classical multiple imputation methods will be used for an additional sensitivity analysis if any of the included variables has more than 5% missing observations. The GEE is a technique which produces unbiased estimates under the assumption that missing observations will be missing at random. An amended approach of weighted GEE will be employed if missingness is found not to be at random. We will perform residual analysis to assess model assumptions and goodness-of-fit.

Generalized linear modelling will be used for outcome variables that are not repeated to create regression models with distribution of the binary and ordinal dependent variables.

The Bonferroni method will be used to appropriately adjust the overall level of significance for multiple comparisons. Count variables will be analyzed using the Poisson regression model. Qualitative variables from the semi-structured interviews will be analysed for their thematic content. The Pearson chi-square test will be used to detect associations between categorical variables, and the mean and standard deviation will be presented for normally distributed continuous variables.

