Key Secondary Outcomes	Bayley scales of infant and toddler development third edition, BSID-III	24 months corrected age	Child assessment
	Behavior Rating of Executive Function Parental version BRIEF-P	24 and 36 months corrected age	Parent questionnaire of child behavior
	Alberta Infant Motor Scale, AIMS	3 and 12 months corrected age	Observation and assessment of child motor development
	Hospital anxiety and depression scale, HADS	12, 24 and 36 months corrected age	Parent questionnaire of depressive symptoms
	State/trait anxiety inventory, STAI	12, 24 and 36 months corrected age	Parent questionnaire of symptoms of anxiety
	Parental self-efficacy scale, PSE	12, 24 and 36 months corrected age	Parent questionnaire of parental self-efficacy
	Resilience scale, RES	12, 24 and 36 months corrected age	Parent questionnaire of parental self-efficacy
Ethics Review	SPIBI has been approved by the Regional Ethical Review Board in Stockholm ref. 2017/1596–31.		
	Date of Approval 26th of October 2019.		
	Contact: [name], scientific secretary, [contact] [name]		
Completion date	Last day of recruitment: 31st of August 2020 (anticipated), may be later if target is not reached yet.		
	Last visit: 31st of August 2021 (anticipated) or 1 year after the ast participant has been recruited.		
	Data collection completion: 1st of September 2023 (anticipated)		
Summary Results	No results yet		
IPD sharing statement	Undecided		

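### Plain Bonferroni for the secondary outcomes is valid but dominated: Holm's step-down method controls the same family-wise error and never rejects less

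*Protocol article*

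**What the plan says.** The Statistical analysis plan section prescribes "separate testing with multiplicity adjustments for secondary outcomes" and names the method: "The Bonferroni method will be used to appropriately adjust the overall level of significance for multiple comparisons". I read the two together as plain, single-step Bonferroni over the secondary outcomes. On alpha it says "The level of significance is specified at 0.05". It does not say which tests form the family or how many there are. For repeated continuous outcomes the same section plans a linear mixed model, which could give one test per scale instead of one per visit.

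Outcome measurements and the Key Secondary Outcomes rows of the registration table list seven secondary instruments: BSID-III, BRIEF-P, AIMS, HADS, STAI, PSE and RES. Several have more than one scale and more than one age. For example, the registration table lists "Behavior Rating of Executive Function Parental version BRIEF-P" at 24 and 36 months corrected age, and Outcome measurements says that all five of its subscales "will be used, and the hypothesis is that the intervention group will have fewer executive problems reported".

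The only effect size is in Sample size and statistical power, in these words: "the effect size of the intervention on the primary outcome measure Emotional Availability Scales (EAS) will be moderate, i.e., Cohen’s d = 0.5". That section continues: "we aim to recruit 130 participants, which gives us a power of 0.8 given a normal distribution and an alpha value of 0.05". No effect size or power is given for any secondary outcome.

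**The concern.** Bonferroni compares every p-value with alpha divided by the number of tests. With many scales and ages the threshold becomes very small, and a moderate real effect can easily miss it. Child development and parental mental health are two of the three domains in the Aims, and in this trial they are assessed through the secondary outcomes. The Discussion makes a case for wider introduction if there are effects on interaction, child development and/or parental mental health. A needlessly strict testing rule therefore bears on conclusions that the authors intend to draw. A rule with the same error guarantee that never rejects less is available.

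**Working it through.** **Inputs.** N = 130, with "50% of which will be randomized to the SPIBI intervention", so 65 per arm. Alpha is 0.05, taken as two-sided because the article does not state sidedness. d = 0.5 is stated for EAS only; using it for secondary outcomes is an assumption. No loss is assumed, since no dropout rate is given.

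**The plan's own figure.** The noncentrality is d × √(n/2) = 0.5 × √32.5 = 2.850. Normal-approximation power is Φ(2.850 − 1.960) = 0.813. The noncentral t gives 0.808, and Mann-Whitney (relative efficiency 0.955) gives 0.789. The stated 0.8 is reproduced. A one-sided t-test would give 0.883, so the figure is a two-sided one.

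**Possible family sizes from the listed outcomes.**
- Every scale at every post-baseline age: BSID-III 3, BRIEF-P 5 × 2 = 10, AIMS 2, HADS 2 × 3 = 6, STAI 2 × 3 = 6, PSE 3, RES 3. Total 33.
- One mixed-model test per scale: 3 + 5 + 1 + 2 + 2 + 1 + 1 = 15.
- One test per instrument: 7.

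**Per-test power under Bonferroni**, each test at 0.05/m, d = 0.5, 65 per arm:

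| m | alpha per test | normal | t | Mann-Whitney |
|---|---|---|---|---|
| 33 | 0.00152 | 0.374 | 0.353 | 0.329 |
| 15 | 0.00333 | 0.466 | 0.447 | 0.421 |
| 7 | 0.00714 | 0.564 | 0.548 | 0.522 |

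If 10% to 20% were lost (an assumption), the t-test figure for m = 33 would fall to 0.299 and 0.247.

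**Why Holm cannot do worse.** Order the p-values. Holm compares the j-th smallest with 0.05/(m − j + 1) and stops at the first failure. Each of these thresholds is at least 0.05/m, so every Bonferroni rejection is also a Holm rejection. For the error rate, let m₀ hypotheses be truly null. A first false rejection needs the smallest null p-value to be at most 0.05/m₀. The chance of that is at most m₀ × 0.05/m₀ = 0.05, with no assumption about dependence.

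**Size of the gain.** Both rules were applied to the same simulated test statistics: 40,000 runs, normal, equal correlations of 0, 0.3 and 0.5. The figures are average power per real effect.

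| m | Bonferroni | Holm, 1 real | Holm, about half real | Holm, all real |
|---|---|---|---|---|
| 33 | 0.37–0.38 | 0.37 | 0.40 (16 real) | 0.44–0.47 |
| 15 | 0.47 | 0.47 | 0.49 (7 real) | 0.57–0.58 |
| 7 | 0.56–0.57 | 0.56–0.57 | 0.59 (3 real) | 0.67–0.69 |

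Holm's family-wise error was at most 0.048 in every scenario, and no Bonferroni rejection was lost in any run.

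**The case against.** Bonferroni is valid under any dependence and conservative, so nothing is wrong in the sense of bias or false positives. That stands, and it limits the point to an avoidable inefficiency.

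A reader might infer that the plan tests 33 hypotheses with about one-third power for its planned effect. The documents do not support that. They fix no family: 33 is the finest split of the key set, the planned mixed model could reduce it to 15, and testing both parents' scores or the other listed outcomes could enlarge it. The d = 0.5 belongs to EAS alone. Leaving the exact family to a separate analysis plan is also usual.

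A reader might also infer that Holm cures the loss of power. It does not. With 33 tests, average power stays below one half even if every effect is real, and with few real effects Holm and Bonferroni are almost the same. Moving from 33 tests to 7 under Bonferroni (0.37 to 0.56) gains more than moving from Bonferroni to Holm at any fixed family size examined. But cutting the family demotes scales and ages that the article lists, and the documents do not rank them, so it is a trade-off and not a correction.

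Nor is Holm entirely free. Bonferroni comes with simple simultaneous confidence intervals that do not carry over directly. Holm also needs all p-values of the family before its extra rejections can be settled, and these outcomes run from 3 to 36 months corrected age. Results at or below 0.05/m could still be declared as they arrive, as under Bonferroni.

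**Conclusion.** The point holds as an improvement to a stated choice. As a testing rule, plain Bonferroni is dominated by Holm, and that conclusion depends on neither the family nor the effect size. The size of the benefit does depend on them. With d = 0.5 on the secondary outcomes, 65 per arm, no loss and equally correlated test statistics, the gain runs from near zero when few effects are real, through about 2 to 3 points when about half are, to about 7 to 12 points when all are. Per-test power under Bonferroni lies between about 0.35 and 0.56 across the three family sizes, slightly lower with Mann-Whitney, and Holm alone does not bring any of them to 0.8. The adjustment is tied to the secondary outcomes, so the power stated for the primary outcome is not in question here.

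**What to change.** In the Statistical analysis plan section, replace the Bonferroni method by the Holm step-down method for the secondary outcomes. Report unadjusted 95% confidence intervals, labelled as such, beside the Holm-adjusted p-values.

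The cost is wording only. No data collection, sample size or model changes, and the adjusted p-values follow from the list of unadjusted ones: multiply the j-th smallest by (m − j + 1), carry the running maximum forward and cap at 1. What is given up is the simple simultaneous interval, and final decisions for results between 0.05/m and their Holm threshold wait until the family is complete.

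Restricting the confirmatory family to fewer scores or ages would recover more power, but at the price of fewer confirmatory claims. That is an option for the sponsor to weigh, not a required change.

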Swedish data show that approximately 2/3 of the EPT children have no or mild impairment, while 1/3 have moderate to severe neurodevelopmental impairments when entering primary school [4], with signs thereof already in preschool [5]. EPT children are a defined high-risk population, and the occurrence of cognitive impairment [1] increases the earlier in pregnancy the child was born [17]. Working memory [18] and executive functions [3, 19, 20] seem to be particularly vulnerable in extremely preterm children, and Attention Deficit Hyperactivity Disorder (ADHD) is twice as common among EPT children compared to term peers [21]. Executive function (EF) deficits are of particular developmental interest, since self-regulation is associated with EF [22], and EPT children tend to display early self-regulatory difficulties [23]. Another neuropsychiatric disorder overrepresented among EPT children is autism spectrum disorder (ASD), which is diagnosed in 17% of EPT children. In some studies, up to 29% of EPT children screen positive according to ASD observation protocols [24–26]. Moreover, several skills that are important for school success, such as mathematical [27] and linguistic abilities [28, 29], are negatively affected by extreme prematurity; preterm-born students in general do not perform at the same level as their term classmates in school [30–32]. Additionally, EPT children have an increased risk of mental illness [33, 34] and of being bullied throughout school [35]. Given the described outcomes of extreme prematurity, there is a clear need for interventions and treatments that may positively influence the long-term development of EPT children.

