Parental depression will be measured by Hospital Anxiety and Depression Scale (HADS) [72, 73] at term age and at 12, 24 and 36 months corrected age. On the HADS, the range for the depression subscales is 0–21, and the range for the anxiety subscales is 0–21. It is hypothesized that lower scores will be observed for the parents of the children in the intervention group.

Parental anxiety will be measured by the State-Trait Anxiety Inventory (STAI) [74] at term age and at 12, 24 and 36 months corrected age. Both the state and trait scales have a maximum score of 80 points. It is hypothesized that lower scores will be observed for the parents of the children in the intervention group.

Parental self-efficacy will be measured by the Parental Self-Efficacy Scale (PSE) [75] at term age and at 12, 24 and 36 months corrected age. The PSE has 24 items for children at term age and at 12 and 24 months corrected age, while it has 48 items for children of older ages. All items are rated on a 0–10 scale. It is hypothesized that higher scores will be observed for the intervention group at 12, 24 and 36 months corrected age.

Parental resilience will be measured by the Resilience Scale (RES) [76, 77] at term age and at 12, 24 and 36 months corrected age. The RES is a 25-item scale with a 7-point Likert scale. It is hypothesized that higher scores will be observed in the intervention group.

The *other outcome measurements* are listed below. The Hammersmith Neonatal Neurological Outcome (HNNE) is used at term age as a baseline measurement. Post discharge neurological development will be assessed with the Hammersmith Infant Neurological Examination (HINE) [78–80] at 3 months, 12 months, and 24 months corrected age. It is hypothesized that higher scores will be observed for the intervention group. The HINE can be used for infants 2–24 months of age and has optimal scores as well as cut-off values for future less fortunate motor outcomes. It includes 26 items assessing posture, movements, muscle tone, cranial nerve reflexes and reactions, with a score range of 0–3 for each time, thus yielding a possible sum of 0–78 points.

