Children’s motor development will be measured using Peabody Developmental Motor Scales (PDMS) [81] at 12 months corrected age. It is hypothesized that higher scores will be observed for the intervention group. The ranges for each subscale are as follows: stationary, 0–42; locomotion, 0–138; object manipulation, 0–30; grasping, 0–44; and visual-motor integration, 0–113. It is hypothesized that higher scores will be observed for the intervention group.

Children’s neurological development will be measured using the General Movement Assessment (GMA) scale (normal-absent fidgety) at 3 months corrected age [82–84].

Children’s general development will be measured using the Ages and Stages Questionnaire (ASQ-R) [85–87] at 12, 24, and 36 months corrected age. It is hypothesized that the parents of the children in the intervention group will score their children higher. All five subscales (communication, gross motor, fine motor, problem solving, personal-social) will be used, with an overall score ranging from 0 to 300. It is hypothesized that higher scores will be observed for the intervention group.

Children’s strengths and difficulties will be measured using the Strengths and Difficulties Questionnaire (SDQ) [88, 89] at 24 and 36 months corrected age, with the hypothesis that fewer difficulties and more strengths will be scored by parents in the intervention group. The SDQ consists of 25 items on a 3-point scale: 5 items on prosocial behaviour and 20 questions about various difficulties. It is hypothesized that higher scores will be observed for the intervention group for prosocial behaviour and that lower scores will be observed for the intervention group on the problematic subscales.

Child’s autistic symptoms will be measured using the Modified Checklist for Autism in Toddlers (M-CHAT) [90] at 24 months corrected age. The scale ranges from 0 to 20 points, and it is hypothesized that lower scores will be observed for the intervention group.

Infant temperament is measured using the Infant Behaviour Questionnaire (IBQ-R) [91, 92] at 12 months corrected age. The IBQ-R consists of 37 items on a 7-point scale, and it is hypothesized that less problematic behaviour will be observed for the intervention group, i.e., the intervention group will have higher scores on smiling, laughter and soothability subscales and lower scores on the fear and distress to limitations subscales.

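### Poisson regression is named for count variables without saying which outcomes these are, and with no provision for overdispersion or for a failed fit check

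*Protocol article*

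**What the plan says.** The Statistical analysis plan section gives one sentence on counts: "Count variables will be analyzed using the Poisson regression model". It adds no dispersion parameter, robust variance or substitute distribution, and it does not say which variables it covers.

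Four other statements in the same section bear on it:

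- Model checking is planned: "We will perform residual analysis to assess model assumptions and goodness-of-fit". Nothing is said about what follows from a poor fit.
- A general two-group test is named: "Comparisons between the two groups will be performed with Mann-Whitney U test for independent samples".
- For outcomes measured once: "Generalized linear modelling will be used for outcome variables that are not repeated". That sentence goes on to speak of binary and ordinal dependent variables.
- "The level of significance is specified at 0.05", with a Bonferroni adjustment. Neither the sidedness nor the number of tests is stated.

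M-CHAT, the autism checklist, is measured once, at 24 months corrected age. The Outcome measurements section says of it: "The scale ranges from 0 to 20 points, and it is hypothesized that lower scores will be observed for the intervention group". It appears in the group introduced by "The *other outcome measurements* are listed below", below the primary and secondary tiers, although the Hypotheses section includes autistic symptoms in the secondary hypotheses on the children.

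**The concern.** Poisson regression takes its standard error from the fitted mean. Where scores vary between children by more than the mean implies, the standard error is too small, the confidence interval too narrow and the false-positive rate above its nominal level. Symptom counts often behave this way, because a child who shows one symptom is more likely to show others.

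M-CHAT is the listed outcome that most resembles such a count. If it were analysed with unscaled Poisson standard errors, a chance difference in autistic symptoms could be reported as an effect more often than 5% of the time. The planned residual check might reveal the problem, but with no consequence stated the replacement model would be chosen after the data were seen.

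**Working it through.** **Plan's own figure.** The article gives no design figure for any count outcome. Its only one is power of 0.8 for the primary outcome with 130 participants, half per arm, d = 0.5 and alpha 0.05. The normal approximation gives 0.5 × √(65/2) − 1.96 = 0.890, so power is Φ(0.890) = 0.813; the t-test gives 0.808. The stated figure is reproduced and does not depend on the count model.

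**Inputs.** Alpha of 0.05 and 65 per arm come from the article. A two-sided test is assumed. The variance-to-mean ratio φ is an assumption, because the article gives no mean, SD or dispersion for any count; hence a range.

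**Formula.** If the variance is φ × mean, the model standard error divided by the true one is 1/√φ. The true rejection rate under no effect is then 2 × [1 − Φ(1.96/√φ)].

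| φ | SE ratio | 1.96/√φ | True type I error |
|---|---|---|---|
| 1 | 1.000 | 1.960 | 0.050 |
| 1.5 | 0.816 (18% too small) | 1.600 | 0.110 |
| 2 | 0.707 (29% too small) | 1.386 | 0.166 |
| 3 | 0.577 (42% too small) | 1.132 | 0.258 |

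**Simulation check.** Negative binomial counts capped at 20, with mean 1, 2 or 3, 50 or 65 per arm and 40,000 trials per setting, gave 0.105–0.110, 0.162–0.168 and 0.252–0.256 for φ = 1.5, 2 and 3.

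**Effect of the 0 to 20 bound.** Treat the score as 20 yes/no items with assumed mean 2, so p = 0.1. With correlation ρ between items within a child, φ = (1 − p)(1 + 19ρ).

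- ρ = 0: φ = 0.9 × 1 = 0.90, simulated type I error 0.037 (conservative).
- ρ = 0.05: φ = 0.9 × 1.95 = 1.76, simulated 0.137.
- ρ = 0.10: φ = 0.9 × 2.9 = 2.61, simulated 0.222.

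The bound alone makes the test slightly conservative; modest correlation between items reverses that.

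**Bonferroni.** Seven tests are used for illustration, matching the seven key secondary instruments in the summary table near the end of the article. The level is 0.05/7 = 0.0071. At φ = 2 the true rate is 0.057, and 0.057/0.0071 is about 8 times the intended level. A smaller alpha does not correct a wrong standard error.

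**After correction.** Across φ from 1 to 4, with 50 or 65 per arm, Pearson-scaled standard errors held the simulated type I error at 0.047–0.052. Sandwich standard errors gave about 0.052–0.070, the highest value being at 50 per arm, mean 1 and φ = 4.

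**The case against.** The strongest reply is that nothing ties the Poisson sentence to a known overdispersed outcome. A reader might infer that M-CHAT is to be analysed by Poisson regression, but the article calls it a scale with a range of points, never a count. Mann-Whitney U, which assumes no relation between variance and mean, is named for group comparisons, and generalized linear modelling is named for outcomes measured once. This stands: M-CHAT is a candidate only.

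A reader might also take the Background as evidence of overdispersion, since it reports ASD diagnosed in 17% of extremely preterm children and, in some studies, "up to 29% of EPT children screen positive according to ASD observation protocols". Those are proportions of children from other studies, not distributions of M-CHAT scores. Assuming a low-scoring majority and a high-scoring minority can produce large inflation, but its size then comes from the assumed subgroup means. Nor does the text mention multiple births, so it gives no basis for an argument from sibling clustering.

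Third, the section plans residual and goodness-of-fit checks, and a condensed article may leave the scale parameter or robust variance to a full analysis plan. This limits the weight of the point but does not remove it. The article positively names a model, ties no action to the check, and leaves two tests available for the same outcome with no rule between them.

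**Conclusion.** The point holds as a minor one. Poisson regression is fixed for unnamed count variables with no protection against overdispersion. If φ is 1.5, 2 or 3, a nominal two-sided 5% test rejects about 11%, 17% or 26% of the time under no effect; if φ is 1 or a little below, it is valid or slightly conservative. These rates rest on assumed φ and on unscaled model-based standard errors.

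The documents do not support saying that M-CHAT will be tested this way, or that its false-positive rate will be inflated by a known amount. If it is tested this way, the effect is confined to an outcome in the lowest tier that supports the autistic-symptom hypothesis. The emotional availability outcome and the 130 participants are unaffected.

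**What to change.** Replace the sentence with: *Count outcomes are analysed with a log-link Poisson model using Pearson-scaled standard errors*, or the same with *robust (sandwich)* in place of *Pearson-scaled*. Choose one before the data are seen. Pearson scaling was closer to nominal in the settings above but takes the variance as proportional to the mean; the sandwich form does not need that and was slightly liberal in the smaller, low-mean settings.

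Name the count outcomes, and state whether M-CHAT is analysed by this model or by Mann-Whitney U.

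The cost is two sentences and, when overdispersion is present, wider confidence intervals on the log scale: by √1.5 = 1.22 at φ = 1.5, √2 = 1.41 at φ = 2 and √3 = 1.73 at φ = 3. That extra width is the uncertainty that the unscaled model leaves out.
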